## Abstract

**Background:**

Gallstone disease is a major global health concern with a steadily increasing prevalence, affecting approximately 7% of the global population and imposing substantial health and economic burdens. Globally, gallstone disease accounts for 10–15% of all gastrointestinal hospital admissions, with annual direct medical costs exceeding $6 billion in the United States and ¥20 billion in China, primarily driven by cholecystectomy and post-surgical complications. According to clinical observations, oral administration of olive oil may facilitate the expulsion of small gallstones; however, high-quality evidence supporting this dietary therapy remains limited. In our preliminary study, a 6-day regimen of orally administered functional fatty acids effectively promoted the elimination of small gallstones.

**Objective:**

This study aims to evaluate the efficacy and safety of oral functional fatty acid supplementation for facilitating the expulsion of small gallbladder stones, and to assess its potential as a noninvasive therapeutic option. The primary endpoint is the complete expulsion rate of small gallbladder stones at day 3 post-intervention, confirmed by two independent blinded ultrasound technologists. The complete expulsion rate at day 6 post-intervention is designated as a key secondary endpoint.

**Methods:**

This prospective, single-center, double-blind, randomized controlled trial will enroll 100 adult patients with ultrasonographically confirmed small gallstones (maximum diameter <2 mm) and no prior treatment history. Participants will be randomly assigned at a 1:1 ratio to either the intervention group (*n* = 50), which will receive 50 mL of functional fatty acids daily on an empty stomach for 6 consecutive days, or the control group (*n* = 50), which will receive placebo for the first 3 days followed by the same dose of functional fatty acids for the subsequent 3 days. Abdominal ultrasound examinations will be performed on days 3 and 6 post-intervention to assess gallstone expulsion. Adverse events, including nausea, vomiting, abdominal pain, diarrhea, and signs of biliary obstruction, will be closely monitored throughout the study period.

**Discussion:**

If proven effective, this intervention could provide a noninvasive alternative to surgery for patients with small gallstones, inform clinical practice, and help reduce the healthcare burden associated with gallstone disease.

**Clinical trial registration:**

ClinicalTrials.gov, identifier: NCT06699030

## Introduction

### Background and rationale

Gallstone disease is a significant global health issue (1) that affects approximately 7% of the population, with prevalence increasing steadily in both developed and developing countries (2). This trend has led to substantial health and economic burdens: globally, gallstone disease accounts for 10–15% of all gastrointestinal hospital admissions, with annual direct medical costs exceeding $6 billion in the United States alone and ¥20 billion in China (3–5). These costs are primarily driven by cholecystectomy procedures, which represent the most common abdominal surgery performed worldwide, as well as the management of post-cholecystectomy complications (e.g., persistent abdominal pain, diarrhea, recurrent common bile duct stones) and long-term healthcare utilization (6, 7).

The strategies for treating gallstones are typically categorized into asymptomatic and symptomatic strategies on the basis of their symptoms (8, 9). For asymptomatic gallstones, ursodeoxycholic acid is typically employed to achieve medical litholysis; however, its efficacy is often limited (10, 11). Symptomatic gallstones typically require cholecystectomy, which is generally considered safe but is associated with possible long-term complications, including persistent abdominal pain, diarrhea, and an increased incidence of common bile duct stones (12–14). In addition, surgical interventions are financially and physically burdensome for some patients.

Gallbladder sludge is typically asymptomatic and is most often detected on ultrasound. If left untreated, it can develop into small gallstones measuring less than 2 mm in diameter; in turn, these gallstones can gradually grow and become symptomatic, thus necessitating surgical intervention (15–17). In this study, we define small gallbladder stones as gallstones with a maximum diameter <2 mm, which are also referred to as gallbladder microlithiasis. This term will be used consistently throughout the manuscript to describe our target population.

In our pilot study conducted from April to June 2024 (approved by the Ethics Committee of the First Hospital of Lanzhou University), we enrolled 20 patients with ultrasound-confirmed small gallstones (diameter <2 mm) who received 50 mL of functional fatty acids daily for 6 days. The results showed that 5 (25%) patients achieved complete gallstone expulsion at day 3, and 6 (30%) patients achieved complete expulsion at day 6. No serious adverse events were reported; only 2 patients experienced mild, self-limiting diarrhea that resolved without intervention. The compliance rate (defined as intake of ≥80% of the planned dose) was 100% (18).

Based on these pilot findings, we selected a 6-day intervention duration and established day 3 and day 6 as the primary observation time points, as most stone expulsion events occurred within this window. Additionally, the 25% complete expulsion rate at day 3 in the pilot study was used as the basis for our sample size calculation.

The underlying mechanism may involve greater gastrointestinal motility and increased secretion of cholecystokinin, which promotes gallbladder contraction and facilitates stone expulsion (12, 19–21). However, the limited sample size, absence of a control group, and uncertainty regarding the optimal dose and duration of treatment highlight the need for further investigations to validate these findings.

The aim of this study is to evaluate the efficacy of functional fatty acids as a noninvasive treatment for the expulsion of small gallstones. All participants will provide written informed consent prior to enrollment, and the study will be conducted in accordance with the Consolidated Standards of Reporting Trials (CONSORT) guidelines.

### Aims and objectives

Our aim is to evaluate the efficacy and safety of oral functional fatty acids as a potential nonsurgical approach for promoting the expulsion of small gallstones.

Our specific primary objective is to compare the complete expulsion rate of small gallbladder stones at day 3 post-intervention between the two groups, as confirmed by two independent blinded ultrasound technologists. A key secondary objective is to compare the complete expulsion rate at day 6 post-intervention to evaluate the effect of treatment duration.

In addition, we will determine the incidence and severity of treatment-related adverse events (such as gastrointestinal symptoms and abdominal pain) in the treatment group according to the Common Terminology Criteria for Adverse Events (CTCAE) Version 5.0. In addition, we will evaluate the safety of the oral functional fatty acids by measuring changes in key biochemical markers before and after the intervention, including serum alanine transaminase (ALT), aspartate transaminase (AST), and total cholesterol. ALT and AST are sensitive markers of hepatocellular injury, and their measurement is necessary to assess whether oral administration of large volumes of fatty acids imposes excessive metabolic burden on the liver. Total cholesterol levels will be monitored to detect any adverse effects on lipid metabolism, as well as to evaluate potential changes in bile lipid composition that may contribute to gallstone formation or dissolution.

### Trial design

This is a parallel-group randomized controlled superiority trial with a 1:1 allocation ratio, not a cross-over design. The control group receives placebo for the first 3 days followed by functional fatty acids for the subsequent 3 days. The primary comparisons are: (1) between the experimental group (3 days of functional fatty acids) and the control group (3 days of placebo) at day 3; and (2) between the experimental group (6 days of functional fatty acids) and the control group (3 days of placebo + 3 days of functional fatty acids) at day 6.

This delayed-intervention design was chosen over a 6-day placebo-controlled design primarily for ethical reasons. Our pilot study demonstrated a 25% complete expulsion rate at day 3 with functional fatty acid treatment, and withholding a potentially effective intervention for the full 6 days would be ethically questionable. Additionally, this design allows us to evaluate both the short-term efficacy of the intervention (day 3 comparison: active treatment vs. placebo) and the effect of treatment duration (day 6 comparison: 6 days of continuous treatment vs. 3 days of delayed treatment). Importantly, the day 6 comparison is not between active treatment and placebo, but between two different durations of active treatment.

The core objective of this superiority design is to demonstrate that oral functional fatty acids (experimental intervention) are significantly more effective than the control intervention in promoting the expulsion of small gallbladder stones. This design was selected on the basis of the research hypothesis of the trial: preliminary evidence from preclinical studies and pilot data suggests that compared with the control intervention, functional fatty acids improve gallbladder motility and better regulate bile composition, thereby facilitating the passage of small stones.

The trial is being conducted at the First Hospital of Lanzhou University. The analysis will be based on intention-to-treat (ITT) and per-protocol (PP) methods. A minimum of 50 participants per group is needed to achieve 80% statistical power (with a two-sided *α* = 0.05) in detecting a clinically meaningful difference in the primary efficacy endpoint (e.g., the proportion of participants with complete gallstone expulsion within the treatment period). This sample size calculation is consistent with the superiority design, as it is powered to identify a significant between-group difference in favor of the experimental intervention.

Both participants and researchers will be blinded to the group assignments (double-blinding). The statistician conducting the analysis will remain unaware of the groupings, and the trial nurses will administer the oral treatment. Neither the participants nor the researchers will know which intervention each group receives. Unblinding will be permitted only at the time of statistical analysis, after the trial is completed. In case of an emergency (e.g., acute biliary obstruction), unblinding may be permitted to ensure participant safety. In such an event, the time, reason, and person responsible for the unblinding will be recorded promptly, and the trial monitor will be notified. Participants who are subject to unblinding will be excluded from the final efficacy analysis but will remain in the safety analysis.

In this study, gallstones with a diameter of less than 2 mm were selected as the target objects. The diameter of the cystic duct is generally approximately 2–3 mm, and the inner diameter of the common bile duct is 6–8 mm. Stones smaller than these ductal diameters have the anatomical feasibility to pass through. This selection not only allows the evaluation of gallstone expulsion in the early formation stage (where intervention may be most impactful) but also reduces the potential risk of biliary obstruction—an important safety consideration that aligns with the trial’s goal of assessing both efficacy (per superiority design) and safety.

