## Methods

### Primary objective

The primary aim of this study is to determine the effectiveness of oral functional fatty acids in facilitating the expulsion of small gallbladder stones. Upon trial conclusion and researcher and participant unblinding, the pre and postintervention ultrasound examination data will be meticulously analyzed to comprehensively compare the expulsion volume and expulsion rate of gallbladder stones between the experimental group and the control group on the third and sixth days after the intervention through in-depth intergroup comparisons. Moreover, we will perform a detailed analysis of the differences in the expulsion volume and expulsion rate of gallbladder stones within the experimental group to compare the outcomes after a six-day intervention with those after a three-day intervention; relevant data from the control group will be subjected to the same in-depth intergroup analysis.

We hypothesize that the stone expulsion rate among patients in the experimental group who will consume functional fatty acids for 3 days, will be significantly greater than that among patients in the control group who will take placebo over the same period. Additionally, we anticipate that the stone expulsion rate of the experimental group patients who will take functional fatty acids for 6 days will exceed that of the control group patients who will receive placebo supplemented with functional fatty acids. Furthermore, when the experimental group and the control group are compared, the volume of gallstones expelled and the expulsion rate following a six-day intervention are expected to be notably greater than those observed after a three-day intervention.

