### Outcome measures

#### Primary outcome measures

The primary endpoint is the complete expulsion rate of small gallbladder stones at day 3 post-intervention, confirmed by two independent blinded ultrasound technologists. The complete expulsion rate at day 6 post-intervention is designated as a key secondary endpoint. Complete expulsion of small gallstones is defined as the absence of stone echoes in the gallbladder, with uniform anechoic patterns observed on ultrasound images. When stone echoes persist, multiple diameters of the stones will be measured via ultrasound to estimate their volume, which will then be compared with the preintervention volume to evaluate the partial expulsion amount and rate. The same method will be applied 6 days after intervention.

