#### Primary outcome for sample size calculation

The primary outcome used to determine the sample size was the complete expulsion rate of small gallbladder stones at the end of the 6-day intervention period. Stone clearance is defined as the complete disappearance of sedimentary stones confirmed by abdominal ultrasound (the gold-standard imaging method for gallbladder stone assessment in this study), as assessed by two independent ultrasound technologists who are blinded to the treatment assignment. This outcome was selected because it directly reflects the core therapeutic goal of the intervention (i.e., removing small gallbladder stones) and is consistent with primary endpoints used in similar studies of gallbladder stone interventions (22).

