### Statistical analysis

A predefined statistical analysis plan will be followed. All the statistical analyses will be conducted using IBM SPSS (Statistics 30.0.0). A *p* value of less than 0.05 will indicate statistical significance. Categorical variables will be reported as counts and percentages. Continuous variable data will be presented as mean ± standard deviation for normally distributed data, or median (interquartile range, IQR) for non-normally distributed data.

Analyses will be performed on both the intention-to-treat (ITT) population and the per-protocol (PP) population. The ITT population includes all randomized participants who received at least one dose of the intervention. The PP population includes only participants who completed the study protocol without major protocol violations.

The primary analysis will compare the complete expulsion rate of small gallbladder stones at day 3 post-intervention between the two groups using the chi-square test.

Key secondary analyses will include:

Comparison of complete expulsion rates at day 6 post-intervention between the two groupsWithin-group comparisons of changes in gallbladder volume and gallbladder wall thickness from baseline to day 3 and day 6Comparison of the incidence of adverse events between the two groups

For dichotomous variables, the chi-square test or Fisher’s exact test will be used as appropriate. For continuous variables, the independent samples t-test will be used for normally distributed data, and the Mann–Whitney U test will be used for non-normally distributed data.

After the last patient has completed the 30-day follow-up, a blinded endpoint adjudication committee will independently review all primary and secondary endpoint data.

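### Four sections make day-3 complete expulsion the sole primary endpoint, but Trial design, Primary objective and the sample-size outcome say otherwise and need to be aligned

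*Protocol article*

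**What the plan says.** Day 3 alone is primary in four places in the protocol article. Primary outcome measures states: "The primary endpoint is the complete expulsion rate of small gallbladder stones at day 3 post-intervention", and then: "The complete expulsion rate at day 6 post-intervention is designated as a key secondary endpoint". The Abstract says the same. Aims and objectives reads: "Our specific primary objective is to compare the complete expulsion rate of small gallbladder stones at day 3 post-intervention". Statistical analysis agrees: "The primary analysis will compare the complete expulsion rate of small gallbladder stones at day 3 post-intervention", using a chi-square test, with the day-6 comparison listed among the key secondary analyses.

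Three other sections differ.

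- Trial design lists two primary comparisons. Its list opens with the day-3 contrast: "The primary comparisons are: (1) between the experimental group (3 days of functional fatty acids) and the control group (3 days of placebo"). Number (2) in the same list is the day-6 comparison.
- Primary objective, under Methods, sets out to "compare the expulsion volume and expulsion rate of gallbladder stones between the experimental group and the control group on the third and sixth days". It then adds day 6 versus day 3 contrasts within the groups.
- Primary outcome for sample size calculation names the "complete expulsion rate of small gallbladder stones at the end of the 6-day intervention period". Yet Background and rationale says the pilot's day-3 rate of 25% was the basis, and the section on assumed rates gives both arms a figure only at day 3 (8% and 25%).

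The only threshold in Statistical analysis is that a p "value of less than 0.05 will indicate statistical significance". Trial design gives a two-sided alpha of 0.05.

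**The concern.** A reader cannot tell from Trial design, Primary objective and the sample-size section which result decides the trial. This is more than loose wording, because the two days answer different questions. Day 3 compares active treatment with placebo. Trial design itself explains that day 6 compares two durations of active treatment. A positive day-6 result therefore could not stand in for the placebo-controlled claim.

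Three things are at stake:

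- A choice of primary comparison made after unblinding could be defended from one section or another.
- The sample-size statement is attached to a different endpoint from the one the primary analysis tests.
- If Trial design were followed literally, two tests at 0.05 would each be able to declare success.

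**Working it through.** **1. The sections side by side**

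| Section | What is primary |
|---|---|
| Abstract (Objective) | Complete expulsion, day 3; day 6 key secondary |
| Aims and objectives | Complete expulsion, day 3; day 6 key secondary |
| Primary outcome measures | Complete expulsion, day 3; day 6 key secondary |
| Statistical analysis | Day 3, chi-square; day 6 among key secondary analyses |
| Trial design | Day 3 and day 6 comparisons |
| Primary objective | Rate and volume, days 3 and 6, plus day 6 v day 3 |
| Primary outcome for sample size | Complete expulsion at the end of 6 days |

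**2. Does the stated sample size show which day was meant?**

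The plan's base figure is 47 per group, at 80% power and two-sided 0.05. The pooled two-proportion formula is

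n = [1.96·√(2p̄(1−p̄)) + 0.8416·√(p1(1−p1)+p2(1−p2))]² / (p1−p2)²

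- Day 3, 25% v 8%: p̄ = 0.165, so n = (1.96×0.5249 + 0.8416×0.5110)² / 0.17² = 1.4589² / 0.0289 = 73.6, or 74 per group. One- and two-sided variants at 80% power (pooled, unpooled, arcsine, continuity-corrected) run from 56 to 86. None gives 47.
- Day 6: the control rate is 25%, but the experimental rate is given only as above 25%. Taking the pilot's 6/20 = 30% as an assumption, n = (1.96×0.6315 + 0.8416×0.6305)² / 0.05² = 1.7683² / 0.0025 = 1250.7, or 1251 per group. Assumed experimental rates of 50% and 55% give 58 and 41, so 47 would need a rate between them. The plan states no such rate.

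The figure of 47 therefore does not settle the day. Its failure to reproduce is a separate matter. The text on the rates used does settle it: day 3.

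**3. How much the day matters at 50 per group**

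Power = Φ{[√n·(p1−p2) − 1.96·√(2p̄(1−p̄))] / √(p1(1−p1)+p2(1−p2))}

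- Day 3, 25% v 8%: (7.071×0.17 − 1.96×0.5249) / 0.5110 = (1.2021 − 1.0288) / 0.5110 = 0.339. Power is about 63%.
- Day 6, 30% (assumed) v 25%: (7.071×0.05 − 1.96×0.6315) / 0.6305 = (0.3536 − 1.2377) / 0.6305 = −1.402. Power is about 8%.

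**4. False positives if Trial design were followed**

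Assume no arm difference on either day, 50 per group, each day tested at two-sided 0.05, and success on either. Day 6 is nested on day 3: a patient not clear at day 3 clears by day 6 with probability (p6−p3)/(1−p3). The scenario rates are assumptions around the plan's figures, with 400,000 simulated trials each.

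| Clearance day 3 / day 6 | P(at least one p<0.05), uncorrected chi-square |
|---|---|
| 8% / 12% | 7.9% |
| 8% / 15% | 8.6% |
| 8% / 25% | 8.8% |
| 25% / 30% | 7.3% |

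At 8% the expected count is 50×0.08 = 4, where Fisher's test might be used instead. Replacing chi-square with Fisher's test whenever an expected count is below 5 gives about 6.2-7.3% over the same scenarios. With day 3 as the only primary, there is one primary test at 0.05 and nothing to adjust.

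**The case against.** The strongest reply is that the document already has a governing version. The sections that define the outcomes and the analysis rank day 3 as primary and day 6 as key secondary, and the Abstract and Aims agree. The sample-size outcome then looks like an isolated mislabel, recoverable from Background and rationale and from the assumed rates. Much of this stands. A ranking is stated, and it limits the point to an inconsistency. It does not remove it: Trial design and the sample-size section are operative text, and no rule says which section prevails.

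Several stronger readings are tempting but not supported:

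- **The plan breaks its 5% error rate.** This holds only if Trial design or Primary objective overrides Statistical analysis. How key secondary endpoints are protected may be set out in the predefined analysis plan, which is not shown, so the absence of a multiplicity rule here is not itself a fault.
- **Four tests (rate and volume, two days) give 1 − 0.95⁴ = 18.5%.** That assumes independence. Complete expulsion means no residual stone volume, and day 6 is nested on day 3, so independence cannot hold.
- **Volume is a route to primary success.** The Primary objective heading suggests it, but volume is never called a primary endpoint. Primary outcome measures uses it to describe partial expulsion when stones persist, and Statistical analysis names no expulsion-volume test.
- **The power statement in Trial design is another contradiction.** Its reference to expulsion during treatment is offered as an example, and day 3 falls inside that period. It is loose wording.

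The 6-9% also depends on the test and on counting both directions. Fisher's test throughout gives about 2.9-4.5%. False positives favouring the experimental arm are roughly 3.6-4.5% with chi-square, against a nominal 2.5%.

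**Conclusion.** The inconsistency is real and should be corrected before unblinding. Four sections agree on day 3 as sole primary; Trial design, Primary objective and the sample-size outcome do not match them. The consequence is an unclear decision rule and a sample-size statement tied to the wrong day, for two comparisons whose power differs from about 63% (day 3, 25% v 8%) to about 8% (day 6, assuming 30% v 25%) at 50 per group.

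The error-rate consequence is conditional. It is about 6-9% two-sided if both days are tested at 0.05 with success on either, using chi-square or chi-square with Fisher's test at small expected counts. Under the day-3 version there is no inflation of the primary test.

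**What to change.** - **Trial design:** call day 3 the primary comparison and day 6 the key secondary comparison. State that day 6 is tested confirmatorily only if day 3 has p<0.05, and is otherwise descriptive. Word the power statement in the same section as day-3 complete expulsion.
- **Primary outcome for sample size calculation:** change the outcome to the day-3 complete expulsion rate, matching the 8% and 25% used. This corrects the label only; it does not make 47 per group reproducible.
- **Primary objective:** limit it to day-3 complete expulsion. Label expulsion volume and the day 6 versus day 3 expulsion contrasts as secondary or exploratory.
- **Statistical analysis:** leave the gallbladder volume and wall-thickness analyses as they are. They are prespecified as key secondary and are unrelated to this problem.

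The cost is a wording amendment plus ethics committee approval, which Ethics and dissemination requires for changes to outcomes and analyses. The sponsor also gives up the possibility of a positive claim resting on day 6 or on volume alone. No patient procedure changes.

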### Data monitoring

Given the excellent safety profile and short duration of this trial, a formal data monitoring committee (DMC) is not required. However, a dedicated safety monitoring team will conduct weekly reviews of all adverse event data throughout the study period.

Although the risk is low, we acknowledge the possibility that small gallstones may become impacted at the sphincter of Oddi, leading to obstructive jaundice or acute biliary pancreatitis. In such cases, the intervention will be immediately discontinued, and the patient will receive appropriate medical treatment according to standard clinical guidelines.

All serious adverse events will be reported to the Institutional Ethics Review Board within 24 h of occurrence. *Ad hoc* safety analyses will be performed if any unexpected safety signals emerge.

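### Emergency-unblinded participants are dropped from the efficacy analysis, which contradicts the declared ITT analysis and makes the primary comparison depend on a post-randomization event

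*Protocol article*

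**What the plan says.** All references are to the protocol article.

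- **Trial design**, analysis principle: "The analysis will be based on intention-to-treat (ITT) and per-protocol (PP) methods".
- **Trial design**, emergency unblinding: "In case of an emergency (e.g., acute biliary obstruction), unblinding may be permitted to ensure participant safety".
- **Trial design**, consequence for analysis: "Participants who are subject to unblinding will be excluded from the final efficacy analysis but will remain in the safety analysis".
- **Statistical analysis**, population: "The ITT population includes all randomized participants who received at least one dose of the intervention".
- **Statistical analysis**, primary test: "The primary analysis will compare the complete expulsion rate of small gallbladder stones at day 3 post-intervention between the two groups using the chi-square test".
- **Primary outcome measures**, endpoint: "Complete expulsion of small gallstones is defined as the absence of stone echoes in the gallbladder".
- **Data monitoring**, recognised hazard: "small gallstones may become impacted at the sphincter of Oddi, leading to obstructive jaundice or acute biliary pancreatitis".

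The Standardized ultrasound assessment protocol has every image read by two sonographers who do not know the allocation or earlier results, with a third settling disagreements. Data collection and management sets follow-up at one month.

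**The concern.** A participant who was dosed and later unblinded in an emergency belongs to the ITT set under Statistical analysis, yet is outside the efficacy analysis under Trial design. Nothing in the text limits the exclusion to the per-protocol set, so the two sections cannot both be followed.

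The exclusion is also not neutral. It is triggered after randomization, and the one trigger named is a complication that the protocol accepts can follow when a stone moves and becomes impacted. During days 1 to 3 only the experimental arm receives the active product, so exclusions could be unequal between arms in the window of the primary comparison. What is at stake is whether the primary estimate remains a comparison of the groups as randomized.

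A lesser matter is that the set called ITT requires at least one dose. That is a common modified ITT under another name.

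**Working it through.** **1. Who is in and who is out.** Take a participant who is randomized, dosed, has a day-3 scan read blind, and is unblinded on day 5.

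- Statistical analysis: in the ITT set, because at least one dose was taken.
- Trial design: out of the final efficacy analysis, because unblinded.
- Effect: a valid primary outcome, recorded before the unblinding, is discarded. With one month of follow-up and no time limit in the rule, this can happen well after day 3.

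**2. Is the exclusion needed to protect the reading?** The endpoint is read from stored images by sonographers who do not know the allocation. Telling a treating clinician the allocation need not reach them, so the reading remains usable.

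**3. Size.** The plan gives no figure for unblinding, so there is none to reproduce. The number excluded (0 to 5) is an assumption.

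Inputs from the plan: 50 per arm, assumed day-3 clearance of 8% (control) and 25% (experimental), chi-square test, two-sided 0.05. Expected clearances are 50 × 0.08 + 50 × 0.25 = 4 + 12.5 = 16.5 in total, so a few participants carry weight.

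Formula (Pearson, no continuity correction): z = (a/n₁ − c/n₂) / √[p̄(1 − p̄)(1/n₁ + 1/n₂)], with p̄ = (a + c)/(n₁ + n₂).

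First row worked out: p̄ = 15/100 = 0.15; standard error = √(0.15 × 0.85 × 0.04) = 0.0714; z = 0.14/0.0714 = 1.960; p = 0.0499. Control is 4/50 throughout.

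| Active arm | Difference (points) | p |
|---|---|---|
| 11/50, all kept | 14.0 | 0.0499 |
| 11/47, three non-clearers dropped | 15.4 | 0.036 |
| 12/50, all kept | 16.0 | 0.029 |
| 10/48, two clearers dropped | 12.8 | 0.070 |
| 13/50, all kept | 18.0 | 0.017 |
| 13/45, five non-clearers dropped | 20.9 | 0.008 |
| 11/48, two clearers dropped from 13/50 | 14.9 | 0.040 |

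Dropping non-clearers raises the estimate and dropping clearers lowers it.

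**4. Type I error in the one-sided worst case.** Assume equal true rates and remove k non-clearers from the active arm only, by exact binomial enumeration with 50 per arm. The table gives the chance of a significant result favouring active.

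| True rate in both arms | k=0 | k=1 | k=3 | k=5 |
|---|---|---|---|---|
| 25% | 2.54% | 2.92% | 4.05% | 5.07% |
| 8% | 2.35% | 3.07% | 3.29% | 3.29% |

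The inflation is real but modest, and it requires every exclusion to be an active-arm non-clearer.

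**The case against.** The strongest reply is that the rule will seldom operate. Obstruction is given only as an example, unblinding is permitted and not automatic, the limit of less than 2 mm was chosen partly to lower the risk of obstruction, and the pilot saw no serious adverse events in 20 patients. This stands as an argument about size. It does not show absence: 0 of 20 leaves a one-sided 95% upper bound of 1 − 0.05^(1/20) = 13.9%. Nor does it remove the contradiction between the two sections.

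The illustrations are also selective. The 11/50 table starts at the edge of significance and is significant before and after. With 4/50 in control, even five dropped non-clearers do not turn 10/50 (p=0.084) into a significant result (10/45, p=0.051). The only loss or gain of significance in the tables above, 12/50 to 10/48, makes the product look worse. This too stands: the tables show sensitivity, not a demonstrated false positive.

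A reader might go further in four ways that the documents do not support.

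- *Emergency unblinding will mostly follow obstruction caused by the product.* No frequency or cause is given beyond one example.
- *The same obstruction is either dropped or counted as a success.* An obstructed participant who still has gallbladder stones, and is not unblinded, is a failure under the stated endpoint.
- *Obstruction must be scored as non-expulsion.* The endpoint looks only at the gallbladder, so this would redefine it. The choice of estimand is debatable. It would not restore the lost result either: two obstructed clearers rescored as failures turn 12/50 into 10/50, p=0.084.
- *The at-least-one-dose condition is a serious defect.* It is common practice, no rate of undosed patients is given, and the fault is mainly one of labelling.

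**Conclusion.** The point holds in limited form. Trial design fixes an exclusion that contradicts the declared and defined ITT analysis and makes the primary comparison depend on a post-randomization event that treatment can cause. This is a rule stated in the protocol, not a detail left to a statistical analysis plan that is not shown.

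The size cannot be established. It is nil if nobody is unblinded, probably small if events are rare, and of either sign. The illustrations rest on the plan's 8% for control (4/50), on assumed active-arm counts near the planned 25%, on an uncorrected Pearson test, and on an assumed 0 to 5 exclusions, all in the active arm. The documents do not support the inference that the rule will inflate the benefit or hide harm: direction and frequency are unknown, and unblinded participants stay in the safety analysis.

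**What to change.** 1. In Trial design, delete the exclusion from the primary efficacy analysis. State that emergency-unblinded participants stay in their assigned arm with the outcome read by the blinded sonographers. Use their exclusion only in a per-protocol or sensitivity analysis.
2. In Statistical analysis, define ITT as all randomized participants analysed as assigned, and name it as the primary set. Alternatively, label the at-least-one-dose set as modified ITT. This is the minor part.
3. Optional, and not part of the required correction: show a sensitivity analysis that scores duct stones or obstruction as non-expulsion.

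Participants without a day-3 scan fall under the missing-data rule, which may stand in the analysis plan that is not shown.

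Cost: wording only, with no extra patients, visits or scans. The estimate may be slightly less favourable. The change should be made before any allocation is revealed for analysis, because a choice of analysis set made afterwards would be hard to defend.
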